### Randomisation

Within 24 h of birth and once a UAC has been placed in an acceptable position, babies will be enrolled by medical and research staff and randomly allocated in a 1:1 ratio to treatment and placebo groups via a web-based interface maintained and concealed by an independent database controller. Twins will be randomised as separate babies. Randomisation will be stratified for recruitment centre (each centre has different nutrition practices), sex and appropriate-for-gestational-age/small-for-gestational-age status (these variables influence growth and body composition), using blocked randomisation with variable block sizes.

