#### Secondary outcomes

##### Growth

Weight, length and head circumference will be measured at birth, 28 days, 8 and 36 weeks’ postmenstrual age, and at discharge. Weight, height and head circumference will be measured at 2 years’ corrected age. All measurements will be by trained staff using validated, repeatable methods [42, 43]. All growth data Z-scores will be calculated individually for each baby using appropriate normative data. Growth velocity (GV) will be calculated using: GV = [1000 × ln(Wn/W1)]/(Dn ‐ D1) where W = weight (g) and D = day after birth on days n (end of time interval) and 1 (beginning of time interval) [44].

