#### Statistical considerations

##### Sample size

A total of 430 babies (*n* = 215 in each group) will provide 85 % power at a 5 % level of significance (two-sided), to detect an absolute difference of 15 % in survival free of disability between the two groups at 2 years’ corrected age. The sample size has taken into account a 10 % loss to follow up rate and a disability rate in the control group of 50 %.

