##### Statistical analyses

Statistical analyses will be performed on an intention-to-treat basis. Missing outcome data will not be imputed in the primary analysis, as the key assumption of missing at random is not likely to hold in the analysis population. Sensitivity analyses will be conducted, however, using multiple imputations method to explore the potential impact of missing data on outcomes. The characteristics of those participants with missing data will be compared between two treatment groups. Per protocol analysis will be performed for those who received at least 80 % of the intended treatment. Sub-group analysis will be conducted on the treatment outcomes in relation to total protein received and to the extra study dose received. Statistical tests will be two-sided at a 5 % significance level. Twins will be randomised as separate babies, with the non-independence of these pairs taken into account during analysis.

Baseline characteristics of all randomised babies and their mothers will be summarised for each group as well as overall using descriptive statistics. Continuous variables will be reported as numbers of observed and missing values, mean, standard deviation, median and range. Categorical variables will be described as frequencies and percentages. The primary outcome, survival free of disability, will be first presented as unadjusted relative risk (RR) with 95 % confidence interval (CI). Generalised linear regression models appropriate to continuous and categorical outcomes will be used to evaluate the treatment difference between two groups, adjusting for stratification variables and other baseline confounders that are closely associated with the outcomes (e.g. birth weight, sex and treatment with antenatal steroids). Adjusted RRs and 95 % CIs will be estimated using a log link. Analyses of growth outcomes will be performed following completion of NICU discharge assessments but will not be revealed to assessors of the Bayley III at 2 years’ corrected age.

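### Name each growth measure's own birth Z-score as a covariate: it is already collected, and adding it sharpens the head and length comparisons at no cost

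*Protocol article*

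**What the plan says.** Under Statistical analyses, the Protocol article describes generalised linear models for continuous and categorical outcomes, "adjusting for stratification variables and other baseline confounders that are closely associated with the outcomes (e.g. birth weight, sex and treatment with antenatal steroids". The stratifiers, under Randomisation, are recruitment centre, "sex and appropriate-for-gestational-age/small-for-gestational-age status (these variables influence growth and body composition".

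Under Growth, "Weight, length and head circumference will be measured at birth, 28 days" and at later points up to discharge, with weight, height and head circumference again at 2 years' corrected age. All growth data are turned into individual Z-scores, and a weight-velocity formula is also given.

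The Sample size section covers the binary primary outcome only. No standard deviation, correlation or precision target is given for any growth outcome.

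**The concern.** A growth Z-score is size for age. Its natural baseline covariate is usually the same Z-score before treatment, here at birth. The size covariates actually named are birth weight and, through the stratifiers, a yes/no small-for-gestational-age status. With entry limited to below 1000 g, a low weight may reflect very early birth or growth restriction, and a binary flag separates the two only coarsely. Neither says directly how long the baby was or how large its head was.

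This matters most for head circumference and length. The Background rests the rationale largely on early head growth and reports that length benefited less than weight from better nutrition. Because the 430 was not sized for growth, precision for these outcomes depends on the analysis. If the birth value is left out, variance that a recorded baseline could remove stays in the comparison, along with any chance imbalance in birth head or length Z.

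**Working it through.** **1. The plan's own figure.** Inputs from Sample size and Randomisation: power 85 %, alpha 0.05 two-sided, a 15-point difference, control-group disability 50 %, 10 % lost, and equal allocation. With 0.50 v 0.65 and mean 0.575:

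n per arm = [1.960 × √(2 × 0.575 × 0.425) + 1.036 × √(0.50 × 0.50 + 0.65 × 0.35)]² / 0.15² = 193.5.

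Dividing by 0.9 gives 215.0 per arm, 430 in total. (Rounding up at each step gives 194, then 216, or 432.) The stated figure reproduces, and nothing below changes it.

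**2. Value of a baseline covariate.** Adding a covariate with partial correlation ρ to the outcome, given what is already in the model, multiplies residual variance by 1 − ρ². The sample-size equivalent is 1/(1 − ρ²): 4 % more babies at ρ = 0.2, 10 % at 0.3, 33 % at 0.5 and 56 % at 0.6.

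**3. From simple to partial correlation.** Let r be the simple correlation of a measure's birth Z with its later Z. Let R² be the share of birth Z already explained by birth weight and the small-for-gestational-age flag. If those covariates relate to the later value only through birth Z (an assumption), the gain is

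r²(1 − R²)/(1 − r²).

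**4. R² for head circumference (assumed cohort).** The documents give no value, so a cohort was simulated: gestation uniform over 22.5 to 34 weeks, birth weight log-normal with a coefficient of variation of 15 to 18 %, babies of 350 to 1000 g kept, weight Z and head Z correlated 0.6 to 0.8. Birth weight plus the flag explained 44 to 46 % of birth weight Z, but only 15 to 29 % of birth head Z.

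**5. Gain for head circumference, R² = 0.29 to 0.15.**

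| Assumed r | r²/(1 − r²) | Equivalent to more babies |
|---|---|---|
| 0.2 | 0.042 | 3 to 4 % |
| 0.3 | 0.099 | 7 to 8 % |
| 0.4 | 0.190 | 14 to 16 % |
| 0.6 | 0.563 | 40 to 48 % |
| 0.7 | 0.961 | 68 to 82 % |

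**6. If the named covariates carry more.** Should they correlate 0.9 with birth Z (R² = 0.81), the gain falls to 0.190 × 0.19 = 4 % at r = 0.4 and 0.961 × 0.19 = 18 % at r = 0.7.

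**7. If growth would be analysed as change from birth.** With equal variances at birth and later, change has variance 2(1 − r) against 1 − r² after adjustment, before other covariates: 0.60 v 0.51 at r = 0.7 (18 % gain), 0.80 v 0.64 at 0.6 (25 %), 1.20 v 0.84 at 0.4 (43 %). The advantage over change is smaller than the matching r²/(1 − r²) in step 5 when r exceeds 0.5 and larger below that.

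**8. On the outcome scale.** As an illustration with 215 × 0.9 = 193.5 babies per arm and 85 % power, the detectable difference is (1.960 + 1.036) × √(2/193.5) = 0.305 residual SD without the birth value. It is 0.285 at ρ = 0.35 and 0.234 at ρ = 0.64.

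**The case against.** The strongest reply is that the covariate list is open. It is introduced by e.g., and its criterion, close association with the outcome, would admit a measure's own birth Z-score and gestational age. A reader might infer that growth will be analysed without the birth value. The text does not say so, and this part of the reply stands in full. Covariates for each secondary outcome are also commonly left to a statistical analysis plan, which is not shown and may already settle this.

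A second reply is that the size is unknown. That also stands: no correlation appears in the documents, one r will not serve 28 days and 2 years alike, and the result depends on how much the named covariates already carry. No single percentage loss can be attributed to the plan.

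Third, the birth value is partly in use already. The velocity formula starts from an initial weight, and the aims speak of growth from birth. If that means change scores, the gain at high r is well below the top of the range.

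Two further inferences should be resisted. Listing birth among the measurement times does not mean that birth size will be tested as a treatment outcome; it is a schedule. Naming sex as an example when it is already a stratifier is harmless, since it enters the model once.

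What survives is narrow. The examples shown name birth weight and not the measure-specific baseline, growth will be analysed after NICU discharge assessments and so ahead of the primary outcome, and naming the covariate beforehand costs nothing.

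**Conclusion.** This is an improvement available for free, not an error in the plan. Adjusting each growth Z-score for its own birth Z-score gains precision whenever birth size predicts later size beyond birth weight and small-for-gestational-age status. For head circumference the gain is roughly 3 to 80 % more babies for assumed birth-to-later correlations of 0.2 to 0.7. That range rests on the simulated cohort and on the assumption that the named covariates act only through birth head Z; it shrinks if they carry more of birth head Z than simulated. Length was not simulated; the same reasoning applies.

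The point is confined to precision of the secondary growth outcomes. Under randomisation, leaving the covariate out introduces no bias. A reader might infer that the trial is underpowered or the sample size wrong; neither follows, since the 430 reproduces and concerns only the primary outcome.

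**What to change.** In Statistical analyses, add one sentence: each growth Z-score (weight, length or height, head circumference) will be adjusted for the stratification variables, gestational age at birth and the birth Z-score of the same measure. Add a simple rule, fixed in advance, for babies with no birth length or head measurement, so that none is dropped for a missing baseline. If the statistical analysis plan already says this, confirming it is enough.

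The cost is one or two sentences before growth is analysed. Size at birth is already measured, and gestational age must be known to assign the small-for-gestational-age stratum. No extra visits or babies are needed.

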##### Data monitoring and other quality control measures

A Trial Steering Committee has been formed to monitor the conduct of the study. The terms of reference were agreed at the first meeting (before the trial began). Trial procedures will be in accordance with the CONSORT guidelines [48, 49]. The Trial Steering Committee is responsible for advising investigators regarding trial continuation or cessation should issues of futility or safety arise, and meet within a month of all Data Monitoring Committee meetings to consider their recommendations.

The terms of reference for an independent Data Monitoring Committee were agreed at the first meeting. An independent Safety Monitoring Committee has also been formed. During the period of recruitment, aggregated summaries of death or other serious adverse event that the local investigator believes should be referred will be supplied, in strict confidence, to the Safety Monitoring Committee. The Safety Monitoring Committee will review individual reports of adverse events. Group allocation will not be revealed to the Safety Monitoring Committee or the investigators. Should the Safety Monitoring Committee rule that the intervention may have impacted on the adverse outcome, this will be immediately reported to the chair of the Trial Steering Committee. The Steering Committee will decide on the actions to be taken.

## Discussion

This multicentre randomised controlled clinical trial aims to assess whether a higher protein intake in the first 5 days after birth will improve survival free of disability in extremely low birthweight babies. Until data from large, well-designed randomised trials are available to assess the effects of earlier higher intravenous protein intakes it is difficult to develop meaningful, evidence-based nutrition guidelines. A conclusive outcome will provide important, reliable evidence of great relevance for the nutritional management all preterm babies <1000 g at birth in settings where intensive care and intravenous nutrition are provided, because it involves administering additional protein through the simple substitution of one fluid for another using an existing commercial amino acid solution.

This intervention has the potential to improve significantly both short and long-term health outcomes for preterm babies and, therefore, to reduce health costs for these children as they reach adolescence and adulthood. If successful this simple, readily available and low cost intervention is likely to result in a rapid change in international practice, benefiting preterm babies worldwide.

## Abbreviations

ELBW: Extremely low birthweight
UAC: Umbilical arterial catheter
Bayley III: Bayley Scales of Infant Development Third Edition Bayley III
NICU: Neonatal intensive care unit
Z-score: Standard deviation score
MRI: Volumetric magnetic resonance imaging
IQ: Intelligence quotient
CI: Confidence interval
